### Randomization

Randomization codes have been generated and secured by an independent statistician from Centre Hospitalier Universitaire of Caen. The codes have been made available to a Good Manufacturing Practice (GMP) certified clinical trial supply company, which has prepared the treatment packs in accordance with the randomization list. The randomization will be stratified by center and reason for hospitalization.

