#### Secondary endpoints

Secondary endpoints are the of number of PRBC transfused up to 1 month after discharge, cost-effectiveness analysis; the number of patients with grade 3 or 4 bleeding, the number of patients with each complication defined in the primary endpoint, the number of transfusion- related events, number of days with hemoglobin level > 8 g/dL quality of life, duration of neutropenia, the time from randomization to last transfusion, the difference between the hemoglobin level immediately before and the day after transfusion, and the number of transfusion events without respect of the randomization arm. Transfusion-related events are defined as any complication declared by the physician to be related to the transfusion (fever, infection, pulmonary edema, etc.). Quality of life will be assessed using the FACT and QLC30 questionnaires. Neutropenia duration is the time spent with an absolute neutrophil count < 0.5 10^9^/L.

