#### Methodology of the statistical analysis

The number of eligible patients and the number of patients actually included (total and per arm) will be describe in a chart. Qualitative variables will be described as number and percentage, and quantitative variables as number, mean, and standard deviation. Quantitative variables with skewed distribution will be presented as median and interquartile range (25th percentile to 75th percentile). The analysis for the primary endpoint will be conducted in both, intent-to-treat and per-protocol datasets. The difference between randomized arms regarding the primary endpoint will be computed with the corresponding 95 % confidence interval and the appropriate bound will be compared with the non-inferiority margin. All analyses will be stratified by center and reason for hospitalization (blocking factors). If non-inferiority of the experimental arm over the control arm is demonstrated in both the intent-to- treat and per-protocol analyses, superiority tests will eventually be conducted.

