#### Other analysis

Categorical variables will be compared using the χ^2^ or Fisher’s test, as appropriate. Continuous variables will be compared using Student’s *t* test or the Wilcoxon test, as appropriate. The analysis of the overall survival will be adjusted for important stratification and prognostic factors using a multivariate analysis (Cox model). All secondary analyses will be conducted at the bilateral alpha risk of 5 %. Analyses will be performed with SAS version 9.2 (SAS Institute Inc., Cary, NC, USA).

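### The plan says all analyses are stratified, but the tests it names for the secondary endpoints take no strata; as written they are conservative and lose some power for PRBC use

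*Protocol article*

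**What the plan says.** Three places in the protocol article bear on this.

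- Randomization: "The randomization will be stratified by center and reason for hospitalization".
- Methodology of the statistical analysis: "All analyses will be stratified by center and reason for hospitalization (blocking factors"). The sentence carries no restriction to an endpoint.
- Other analysis: "Categorical variables will be compared using the" chi-square or Fisher test, and "Continuous variables will be compared using" Student's t "test or the Wilcoxon test, as appropriate". No strata are named for these tests. The next sentence does name them, for one model only: "The analysis of the overall survival will be adjusted for important stratification and prognostic factors". The level is two-sided: "All secondary analyses will be conducted at the bilateral alpha risk of 5" %.

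The endpoints affected are listed under Secondary endpoints. PRBC use heads the list, and the Abstract defines it as a number of units per patient per hospital stay. The list also contains "the difference between the hemoglobin level immediately before and the day after transfusion", without saying whether the patient or the transfusion is the unit of analysis.

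**The concern.** Chi-square, Fisher, t and Wilcoxon tests in their usual form ignore strata, so a rule that every analysis is stratified and a list of these tests do not agree. A programmer who follows one section departs from the other, and the adjusted or the unadjusted result could be chosen after the data are known.

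The choice matters most for PRBC use. It is the only secondary endpoint named in the Abstract, and the Objective couples non-inferior safety with lower cost. Induction, autologous and allogeneic transplant patients can be expected to differ in how many units they need. Stratified randomization balances those groups between the arms, so they add nothing to the true error of the difference. A test that ignores them still counts their spread as noise. Its standard error is too large, its interval too wide, and its rejection rate below the nominal level.

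**Working it through.** The plan gives no power for PRBC use, so there is no figure of its own to reproduce.

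**Inputs from the article.** 115 patients per arm (Sample size calculation); two-sided 5 % (Other analysis); a reduction of about 25 % in units, from the cited retrospective study (Background and Discussion).

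**Assumptions.** Three equal groups by reason with control means 10, 4 and 6 units; negative binomial counts with variance μ + μ²/4; the same relative reduction in each group; no center effect; reductions of 15 and 20 % as well as 25 %.

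**Step 1, share of variance due to reason (control arm).** The overall mean is 20/3 = 6.67. Between groups: (3.33² + 2.67² + 0.67²)/3 = 6.22. Within groups: (35 + 8 + 15)/3 = 19.33. Share R² = 6.22/(6.22 + 19.33) = 0.24.

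**Step 2, rejection under the null.** With the arms balanced within strata, the unstratified statistic has variance 1 − R², so its true two-sided error is 2[1 − Φ(1.96/√(1 − R²))]. For R² = 0.24 this is 2[1 − Φ(2.25)] = 2.4 %. For R² of 0.1, 0.2, 0.3 and 0.4 it is 3.9, 2.8, 1.9 and 1.1 %.

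**Step 3, power.** Let d be the difference in means, SE_u the standard error the unstratified test uses (between plus within variance of both arms, divided by 115, square root) and SE_t the true one (within variance only). Unstratified power is Φ((d − 1.96·SE_u)/SE_t); adjusted power is Φ(d/SE_t − 1.96).

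| Reduction | d | SE_u | SE_t | Unstratified | Adjusted | Loss |
|---|---|---|---|---|---|---|
| 15 % | 1.00 | 0.625 | 0.545 | 34 % | 45 % | 11 points |
| 20 % | 1.33 | 0.611 | 0.534 | 60 % | 70 % | 10 points |
| 25 % | 1.67 | 0.598 | 0.523 | 83 % | 89 % | 6 points |

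**Step 4, simulation.** Simulating this model (4,000 trials per setting, t test against a linear model with reason) gave, unstratified against adjusted: 2.9 against 5.6 % under the null, 33 against 44 % at a 15 % reduction, 60 against 70 % at 20 %, and 83 against 89 % at 25 %. Other runs of the model put null rejection of the unstratified test at 2.4 to 3.1 % and the power loss at 6 to 11 points.

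**Step 5, a different model.** Normal outcomes in nine equal strata, with strata explaining 0 to 40 % of the variance and a standardized effect of 0.37: the unstratified error falls from 4.9 to 1.2 %, and the power loss rises from 0 to about 9 points (86 against 94 % at the upper end).

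**The case against.** **The sections may not conflict.** The stratification sentence stands between the primary-endpoint confidence interval and the superiority step, so it may cover the primary analysis only. Or it may govern everything, with the later section naming only families of tests whose stratified forms an analysis plan would choose. Either reading is possible, but the text does not settle which. The sentence is unrestricted, and the later section writes adjustment out for survival and not for the tests beside it. On the narrow reading the contradiction goes, but the secondary tests still ignore the factors used to randomize.

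**The effect is small and safe.** This stands. There is no excess of false positives, and at the 25 % reduction the article cites, the unadjusted test still has about 83 % power.

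**Stratifying everything has a price.** This also stands. Three wards (Design) or four (Recruitment and participating centers) times three reasons give 9 to 12 strata. At a 7 % complication rate, 0.07 × 230 ≈ 16 patients have any complication, or 1.3 to 1.8 per stratum, before splitting by component. Strata without events contribute nothing to a Mantel-Haenszel test, and its large-sample approximation is doubtful there.

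**A stronger reading to avoid.** A reader might infer that the PRBC comparison ignores repeated transfusions within a patient. It does not: the endpoint is one count per patient, so the transfusions are already summed. A reader might also put a figure on the hemoglobin change. With an assumed 6 transfusions per patient and correlation 0.1 to 0.3, the design effect 1 + 5·ICC is 1.5 to 2.5, and a test treating transfusions as independent would have a true error of 11 to 22 %. But nothing in the article makes the transfusion the unit of analysis, and a per-patient summary fits its text equally well. That figure is a risk of one possible implementation, not a defect of the plan.

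**Conclusion.** The point holds as an inconsistency in the current text with a modest, conservative consequence. If the named tests are run without strata, the PRBC comparison rejects about 2 to 3 % of the time under the null instead of 5 %. It loses about 6 points of power at a 25 % reduction and about 10 points at 15 to 20 %. These sizes depend on the assumed stratum means and dispersion, which the article does not give, and shrink to nothing if the strata do not differ. The direction follows from stratified randomization alone. The primary comparison, its margin and the 230 patients are untouched. It is worth correcting because it touches the benefit side of the trial's claim, but it threatens no main conclusion.

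**What to change.** Reconcile the two analysis sections in the protocol or analysis plan, before the data are seen.

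- PRBC units, other counts and continuous secondary endpoints: a regression with center and reason as factors (negative binomial or linear), and van Elteren's test where ranks are needed.
- Categorical secondary endpoints with enough events: Cochran-Mantel-Haenszel over the randomization strata.
- Rare single complications: keep Fisher's exact test, and name it as an exception to the stratification rule.
- Hemoglobin change around transfusion: state that the patient is the unit, through one mean per patient or a model with a patient random effect.

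Limiting the stratification sentence explicitly to the primary endpoint would also remove the inconsistency, but would forgo the power. Either way the cost is a few sentences and some programming, with no new data, visits or patients.

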#### Other analysis

Categorical variables will be compared using the χ^2^ or Fisher’s test, as appropriate. Continuous variables will be compared using Student’s *t* test or the Wilcoxon test, as appropriate. The analysis of the overall survival will be adjusted for important stratification and prognostic factors using a multivariate analysis (Cox model). All secondary analyses will be conducted at the bilateral alpha risk of 5 %. Analyses will be performed with SAS version 9.2 (SAS Institute Inc., Cary, NC, USA).

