### Data collection and follow-up

Details of the flowchart and patient follow-up are summarized in Table 1. Each subject who meets the inclusion criteria, verified by the clinician investigator in charge of medical care, will be offered the opportunity enter the study during a meeting in consultation or at first day of hospitalization. The investigator will retrieve the patient consent form at day zero. The following data will be collected at inclusion: vital signs (heart rate, arterial blood pressure, and respiratory rate), weight, and abnormal clinical signs on examination. Quality of Life in Cancer Patients-30 (QLC30), Functional Assessment of Cancer Therapy (FACT) form and EuroQol 5 dimensions (EQ-5D) data will be collected and an electrocardiogram will be performed at inclusion, the end of hospitalization stay and at 1 month after discharge. Creatinine level, blood count and troponin blood level will be collected at inclusion. During the hospitalization stay, blood count and transfusion data will be collected every day until discharge. At the end of the study (1 month follow-up), vital status, and the number of RBP transfused after leaving the hospital and the duration of hospital stay will be recorded. Each complication encountered en route to meeting the primary endpoint will also be recorded.

**Table 1 Tab1:** Flowchart of a patient follow-up

	Screening D-28 to D-1	DO inclusion	At each transfusion	End of hospitalization	One month after hospitalization
Inclusion and exclusion criteria	X				
Patient information	X				
Signed informed consent		X			
QLC30, FACT, EQ-5D questionnaires		X		X	X
Randomization		X			
Clinical assessment		X		X	X
ECG		X			
Laboratory tests – troponin		X			
Biological tests		X	daily	X	X
Transfusion parameters			X		
Complications/Adverse events					X
Alive or dead status					X

*EQ-5D* EuroQol 5 dimensions, *FACT* Functional Assessment of Cancer Therapy, *QLC30* Quality of Life in Cancer Patients-30,D-28 to D-1: day-28 to day -1

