## Discussion

When and how to transfuse patients in intensive care and hematology units remains a key question. Several meta-analysis have been performed in the context of hemorrhagic syndrome, surgery, coronary syndrome, and septic shock. These studies demonstrated that a restrictive transfusion strategy was associated with a reduction of the number of PRBC transfused, as compared to a liberal strategy. This restrictive transfusion strategy was not inferior to the liberal one in terms of mortality, overall morbidity and myocardial infarction. In hematological malignancies, one pilot prospective randomized trial and one retrospective study have compared bleeding events and the number of blood units used with liberal (trigger 12 g/dL) and restrictive ones (8 g/dL). These studies evidenced a reduction of PRBC units transfused in the restrictive arm [11, 12]. Another way to reduce transfusion side effects and the number of transfusions is to reduce the number of RBP transfused at each transfusion in patients with a potential hematological recovery. The single-unit transfusion strategy is not suitable for patients with chronic anemia due to bone marrow failure or myelodysplastic syndrome without therapy. In a retrospective study, Berger et al. demonstrated a 25 % PRBC unit reduction with a substantial cost saving in the intensive care hematology area with a single-unit transfusion strategy compared to historical two units per transfusion [6]. However, no prospective randomized trials have ever been conducted to compare these two strategies (single-unit versus double-unit transfusion), based on the volume transfused rather than on a hemoglobin level trigger. Another question that arises is the duration of the lower hemoglobin level experienced by the group receiving a single PRBC unit. Here, one can argue that patients may experience greater fatigue in this group with a consequent negative impact on quality of life. Therefore, among secondary endpoints of the study, quality of life will be assessed to compare fatigue between the two arms. The aim of this study is to provide a high level of evidence as to whether a single-unit transfusion in patients with transient bone marrow failure is feasible, safe and reduces patient care costs.

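### The tests named for continuous secondary outcomes make no adjustment for the inclusion quality-of-life score, so the fatigue comparison is less precise than the collected data allow

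*Protocol article*

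**What the plan says.** The Data collection and follow-up section of the protocol article lists the questionnaires, including that "Functional Assessment of Cancer Therapy (FACT) form and EuroQol 5 dimensions (EQ-5D) data will be collected", and the same sentence ends with the visit times: "an electrocardiogram will be performed at inclusion, the end of hospitalization stay and at 1 month after discharge". Those times could be read as belonging to the electrocardiogram alone. Table 1 settles it for the questionnaires, which it marks at inclusion, end of hospitalization and 1 month after.

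Quality of life is a secondary endpoint: "Quality of life will be assessed using the FACT and QLC30 questionnaires". The Discussion gives the reason. It raises greater fatigue as a possible drawback of the single-unit arm and answers that "quality of life will be assessed to compare fatigue between the two arms".

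Three statements bear on the analysis:
- Other analysis compares continuous variables by Student's t "test or the Wilcoxon test, as appropriate". The sentence is generic. It does not name quality of life, and it does not say whether the follow-up score or the change from inclusion is tested.
- Methodology of the statistical analysis says: "All analyses will be stratified by center and reason for hospitalization (blocking factors".
- Only one outcome has a named covariate-adjusted model: "The analysis of the overall survival will be adjusted for important stratification and prognostic factors using a multivariate analysis (Cox model".

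The error rate is set by "All secondary analyses will be conducted at the bilateral alpha risk of 5" per cent.

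**The concern.** A score measured before treatment and again at two follow-up visits is the standard setting for a baseline-adjusted analysis. The article names a two-sample test family instead and adds no baseline term. If the follow-up score is tested alone, the information in the inclusion score is unused. If change from inclusion is tested, the inclusion score is used, but less efficiently than it could be.

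This matters more here than for most secondary endpoints. The fatigue comparison is a search for harm from the experimental strategy, in a trial meant to support a non-inferiority claim. A less precise comparison makes a non-significant result more likely, and such a result is easily read as reassurance.

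There is also a mismatch between two sections. One stratifies every analysis by the two blocking factors. The other names tests that, in their ordinary form, stratify by nothing.

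**Working it through.** **Inputs from the documents.** 115 patients per arm (Sample size calculation); two-sided 5 % for secondary analyses (Other analysis); one inclusion and two follow-up measurements (Table 1). The article gives no SD, target difference or correlation for quality of life.

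**Assumptions.** All 115 questionnaires per arm are complete. The correlation r between inclusion and follow-up score, within strata, is 0.3, 0.5 or 0.6. Differences are in units of the within-stratum SD of the score, taken as equal at both times. Power is 80 %.

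**The plan's own figure.** The sample size was set for the primary endpoint, and there is no stated figure for quality of life to reproduce. With 93 % complication-free in both arms, a margin of 10 points, 90 % power and one-sided 5 %:

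n per arm = (1.645 + 1.282)² × 2 × 0.93 × 0.07 / 0.10² = 8.567 × 13.02 ≈ 112, or 224 in total, close to the stated 230.

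Only the 115 per arm is carried forward.

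**Detectable difference, follow-up score alone.**

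(1.96 + 0.842) × √(2/115) = 2.802 × 0.1319 = 0.369 SD

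**With ANCOVA** the residual SD is multiplied by √(1 − r²). **With a t test on change from inclusion** it is multiplied by √(2(1 − r)).

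| r | follow-up alone | change score | ANCOVA | ANCOVA variance ratio, 1 − r² | patients per arm for equal precision without adjustment, 115/(1 − r²) |
|---|---|---|---|---|---|
| 0.3 | 0.37 | 0.44 | 0.35 | 0.91 | 126 |
| 0.5 | 0.37 | 0.37 | 0.32 | 0.75 | 153 |
| 0.6 | 0.37 | 0.33 | 0.30 | 0.64 | 180 |

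**ANCOVA against the change score at any r.** Since 1 − r² = (1 − r)(1 + r) and 1 + r ≤ 2, the ANCOVA variance never exceeds the change-score variance 2(1 − r). Below r = 0.5 the change score is worse than ignoring the inclusion score.

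**In terms of power.** At a true difference of 0.30 SD, the follow-up score alone has 62 % power. ANCOVA has 66 %, 75 % and 81 % at r = 0.3, 0.5 and 0.6.

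**The case against.** The strongest reply is that one generic sentence in a journal article is a default, and that the model for a questionnaire endpoint belongs in an analysis plan that is not shown. Part of this stands: visit-wise contrasts, scoring and missing-data handling may properly sit there, and their absence is no fault. But the article does not leave the method open. It names a test family for continuous outcomes, and each natural use of that family, on the follow-up score or on the change, is at best equal to ANCOVA.

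It is also fair to say that the size rests on an assumed correlation. Inclusion precedes intensive chemotherapy or transplant, so a high correlation with later scores cannot be presumed. At r = 0.3 the gain is only from 0.37 to 0.35 SD. Where stratification is carried out, only the within-stratum correlation counts, and a crude correlation might overstate the gain.

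Four stronger readings are tempting, and the documents do not support them:
- **That the analysis is wholly unadjusted.** The Methodology section stratifies all analyses by center and reason for hospitalization. What is missing is adjustment for the inclusion score.
- **That the inclusion score is certainly unused.** A test on change from inclusion fits the text.
- **That chance baseline imbalance biases the result.** Under randomization the comparison is unbiased on average, and the imbalance is already reflected in its standard error.
- **That the QALY analysis is wrong.** The cost-effectiveness paragraph of the article states no QALY test and no handling of the inclusion utility. That is silence, not an error.

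**Conclusion.** The point holds as a loss of precision on a secondary endpoint that the article itself presents as the answer to a foreseeable objection to the single-unit arm. The comparison as named is valid, and the primary endpoint is not affected. Under the assumptions above, baseline adjustment would lower the detectable difference by about 0.02 to 0.07 SD (0.369 − 0.352 to 0.369 − 0.296), with 0.05 SD at r = 0.5. Incomplete questionnaires would raise every detectable difference shown. The conclusion that ANCOVA is at least as precise as either form of the named t test does not depend on the value of r, apart from a negligible cost for estimating the covariate effects; the size of the gain does. The mismatch between stratifying all analyses and naming plain two-sample tests is a separate, smaller inconsistency that the same change removes.

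**What to change.** In Other analysis, name a method for FACT and QLC30: ANCOVA at each follow-up visit, or a mixed model over both visits, with the inclusion score, center and reason for hospitalization as covariates. Report the adjusted difference between arms with its 95 % confidence interval at each visit, so that a non-significant fatigue result is read with its uncertainty. This also puts into effect the stratification promised in the Methodology section.

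As an optional extension in the same spirit, QALYs can be adjusted for the EQ-5D utility at inclusion by regression.

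The cost is wording in the analysis section or the analysis plan, settled before the data are examined. No new visit, questionnaire or patient is needed.

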### Treatment and study intervention

The study protocol and both arms of randomization are detailed in Fig. 1. Patients randomized in arm A will receive 2 PRBC units if their hemoglobin level is below 8 g/dL during hospitalization and until 1 month after discharge. Patients randomized in arm B (experimental arm) will receive a single PRBC unit if their hemoglobin is below 8 g/dL during hospitalization and until 1 month after discharge. All PRBC units are leukodepleted, and matched according to French policies. Auto-SCT patients will receive irradiated PRBC units and allo-SCT recipients cytomegalovirus (CMV) seronegative irradiated PRBC units [8].

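### The red-cell saving could be estimated more precisely at no cost by adjusting for hemoglobin and weight, both recorded at inclusion but unused in the stated analysis

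*Protocol article*

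**What the plan says.** All references are to the protocol article.

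- **Other analysis** gives one generic rule for continuous variables, Student's t "test or the Wilcoxon test, as appropriate". Prognostic adjustment is named for one outcome only: "The analysis of the overall survival will be adjusted for important stratification and prognostic factors using a multivariate analysis (Cox model").
- **Methodology of the statistical analysis** adds: "All analyses will be stratified by center and reason for hospitalization (blocking factors"). On its wording this reaches the red-cell comparison too.
- **Randomization** uses the same two factors: "The randomization will be stratified by center and reason for hospitalization". Neither hemoglobin nor weight is a stratification factor.
- **Secondary endpoints** lists first the "number of PRBC transfused up to 1 month after discharge". The abstract also presents red-cell use as the secondary endpoint.
- **Data collection and follow-up** records at inclusion "weight, and abnormal clinical signs on examination", and adds: "Creatinine level, blood count and troponin blood level will be collected at inclusion". Hemoglobin is not named there but comes with the blood count.
- **Treatment and study intervention** ties transfusion to a fixed trigger. Patients in the single-unit arm "will receive a single PRBC unit if their hemoglobin is below 8 g/dL during hospitalization", and the two-unit arm has the same threshold.

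**The concern.** A fixed hemoglobin trigger makes two inclusion measurements natural predictors of the unit count. A patient who starts close to 8 g/dL reaches the trigger sooner. A patient in whom each unit raises hemoglobin less, which plausibly depends on body size, returns to it sooner. Both measurements will be in the database, yet the stated comparison uses neither.

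The precision of the estimated red-cell saving is at stake. The Objective section couples non-inferior safety with a cost reduction, the Background rests the trial's value on fewer transfusions and lower cost, and transfusions are a costed item in the economic evaluation. The endpoint is secondary and the trial was not sized on it, but it measures the expected benefit of the single-unit policy. An interval wider than the data allow weakens that part of the conclusion.

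**Working it through.** **1. The plan's own figure.** The only sample size in the article is for the primary endpoint: 93 % free of complications, margin 10 %, power 90 %, alpha 5 %, 115 per group. With one-sided alpha 0.05,

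n per arm = 2 × 0.93 × 0.07 × (1.645 + 1.282)² / 0.10² = 111.5, so 112 per arm and 224 in total.

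This is within 3 % of 230. The figure only supplies the 115 per arm used below. Nothing was sized on red-cell use, and the 230 does not change.

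**2. Inputs for red-cell use.** The article gives 115 per arm, two-sided alpha 5 % for secondary analyses, and a retrospective reduction of about 25 %. It gives no standard deviation (SD) of units, no mean number of units, no SD of inclusion hemoglobin, and no correlation of hemoglobin or weight with units. No absolute gain can be computed. The correlation below is an assumption, shown over a range.

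**3. Precision gain.** Let ρ be the multiple correlation of hemoglobin and weight with units within the strata. In the linear-model approximation, adjustment multiplies the variance of the arm difference by 1 − ρ². Then:

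- standard error (SE) ratio = √(1 − ρ²)
- effective number of patients = 230 / (1 − ρ²)
- power of a comparison that has 80 % without the covariates = Φ[(1.960 + 0.842) / √(1 − ρ²) − 1.960]

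| Assumed ρ | SE ratio | 230 patients worth about | 80 % power becomes |
|---|---|---|---|
| 0.1 | 0.995 | 232 | 80.4 % |
| 0.2 | 0.980 | 240 | 81.6 % |
| 0.3 | 0.954 | 253 | 83.6 % |
| 0.4 | 0.917 | 274 | 86.4 % |
| 0.5 | 0.866 | 307 | 89.9 % |
| 0.6 | 0.800 | 359 | 93.8 % |

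**4. Which ρ is plausible?** Suppose, as an assumption, that each g/dL of starting hemoglobin changes the count by about one unit. Then ρ for hemoglobin alone is roughly (SD of hemoglobin) / (SD of units).

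- Hemoglobin SD 1.0 to 1.5 g/dL and unit SD 3 to 4: from 1.0/4 = 0.25 to 1.5/3 = 0.50.
- Same hemoglobin SD and unit SD 5 to 6: from 1.0/6 = 0.17 to 1.5/5 = 0.30.

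The answer is set by the SDs chosen. These values also ignore the strata, and reason for hospitalization may already carry part of the effect.

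**5. Chance imbalance.** With 115 per arm, the 95 % range of the difference in mean inclusion hemoglobin is ±1.96 × √(2/115) = ±0.26 SD. At a correlation of 0.2, 0.3 or 0.5, this moves the estimated difference in units by up to 0.05, 0.08 or 0.13 outcome SD (0.26 × the correlation). The half-width of the 95 % interval without the covariates is also 0.26 outcome SD, so that interval already includes this variation.

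**The case against.** The case against is substantial.

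- **Scope.** This is a journal article, the analysis plan is not shown, and the covariate list for a secondary endpoint is often left to that plan. The analysis plan may already contain the adjustment. However, the article does not leave the method open: it names the tests and assigns prognostic adjustment to overall survival.
- **The comparison is not wholly unadjusted.** A reader of Other analysis alone might infer that it is. The section on methodology stratifies all analyses by center and reason for hospitalization. The accurate statement is narrower: inclusion hemoglobin and weight are not used. Plain two-sample tests carry no strata, so the two sections do need to be reconciled.
- **There is no validity problem.** A reader might also infer that a chance difference in starting hemoglobin biases the saving. Randomization rules that out. The imbalance is ordinary sampling variation, already inside the interval, and type I error is not inflated.
- **The size is not in the documents.** A firm percentage gain would rest on invented SDs, as step 4 shows.
- **The endpoint may be well powered anyway.** Suppose a saving of 1.5 to 2 units (25 % of an assumed 6 to 8) and a unit SD of 3 to 4. The SE is then SD × √(2/115) = 0.40 to 0.53, and power without the covariates runs from about 81 % to above 99 %. If the covariates explained 13 % of the variance, the worst case would rise from about 81 % to 86 %.

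These points reduce the concern to a modest precision gain on a secondary endpoint. They do not remove it: no section adjusts red-cell use for either measurement, and doing so needs nothing that is not already collected.

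**Conclusion.** The point holds as a free improvement of low severity. The stated analysis is valid, but it leaves available precision unused in estimating the red-cell saving. The size depends on an assumed within-strata correlation: negligible at 0.2 or below, and worth roughly 44 to 77 additional patients at 0.4 to 0.5 (274 − 230 and 307 − 230). The documents cannot show where in that range the trial lies. They do not support calling the planned test biased or wrong, and the primary endpoint and its sample size are unaffected.

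**What to change.** In Other analysis, replace the generic test for this endpoint with a prespecified regression of the number of units on arm, center, reason for hospitalization, inclusion hemoglobin and inclusion weight. Use a variance robust to overdispersion and to unequal spread between arms, since one arm accrues units in twos. Report the adjusted difference in units with its 95 % CI. If a log-link count model is used, obtain that difference by averaging its predictions over the trial population. Keep the stratified test without these two covariates as supportive.

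The same sentence reconciles the named tests with the stratification stated under Methodology of the statistical analysis. Fix it before outcome data are seen by arm. The cost is one sentence in the analysis plan, with no new data, patients or visits.
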